### Planned visit schedule

The visit schedule for all assessments is presented in Table 1.

**Table 1 Tab1:** Data collection methods and clinical assessment time points

Timepoint	Screening	T0	T1	T2	T3
**Enrolment:**					
Signed informed consent		X			
Diagnosis	X				
Randomization		X			
**Interventions:**					
Sham intervention group		X	X		
Active intervention group		X	X		
**Assessments:**					
*Primary outcome*					
HDRS-17	X	X	X	X	X
*Secondary outcomes*					
DADSI		X	X	X	X
RBANS		X	X	X	X
WHODAS 2.0		X	X	X	X
*Adverse effects*					
YMRS	X		X	X	X
Adverse checklist			X		
Pregnancy test	X				
Patients’ compliance			X	X	X
Blinding assessment					X

X represents data collection timepoint

*HDRS-17* 17-item Hamilton Depression Rating Scale, *DADSI* the DSM-5 Anxious Distress Specifier Interview, *RBANS* the Repeatable Battery for the Assessment of Neuropsychological Status, *WHODAS 2.0* the WHO Disability Assessment Schedule 2.0; *YMRS*, the Young Mania Rating Scale

### Statistical analysis

Continuous variables will be summarized using the mean and standard deviation measures. Categorical variables will be presented in terms of frequency and percentage. Between-group comparisons will be assessed using the Mann–Whitney *U* test for continuous variables and either the chi-square test or Fisher exact test for categorical variables. The primary outcome will be analyzed based on the intention-to-treat principle, with worst case imputation applied. For repeated continuous outcomes, a mixed linear model will be employed, which includes the interaction between group (active versus sham) and time (baseline, post-assessment, 2-week and 6-week follow-up assessment.

The hypotheses will be tested using unpaired, two-tailed tests at a significance level of 0.05. The software SAS, v.9.4 (SAS Institute Inc.), was utilized.

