### Eligibility criteria

The inclusion criteria are as follows:Ability and willingness to provide written informed consent for trial participation and undergo all necessary procedures is required;The age range is between 18 and 65 years old;A diagnosis of MDD with ADS according to the Diagnostic and Statistical Manual of Mental Disorders, Fifth Edition (DSM-5), which is assessed by at least one professional psychiatrist; the presence of specifier was evaluated based on DSM-5 criteria, which mandates that MDD patients exhibit at least two out of five symptoms;Han ethnicity;Right-handedness;Adequate auditory and visual acuity to perform requisite inspections;Presence of depressive symptoms ranging from mild to severe, as measured and defined by HDRS-17 scores ≥ 8 and ≤ 52 [16];Willing to remain on maintenance pharmacotherapy for at least 2 weeks before the stimulation initiation and during the total stimulation period.

The exclusion criteria are as follows:The presence of severe systemic illnesses, including but not limited to severe hepatic, renal, endocrine, cardiovascular, respiratory, hematological, or oncological diseases that are deemed by the investigator as unsuitable for participation in the trial;Any laboratory examination that shows clinically significant abnormalities and may have an impact on the health of participants, as determined by the investigator;A history of any significant medical illness, such as neurological disorders (e.g., cerebral trauma, seizure disorder, etc.), that would render the participant unsafe for trial participation in the investigator’s opinion;Known to have current psychosis as determined by the DSM-5 criteria or a history of a non-mood psychotic disorder;Current substance abuse, including alcohol and/or illicit or prescription drugs;Current or planned pregnancy and/or lactation during the trial;A scalp with abnormal conditions, such as open wounds;A score = 4 for item 3 (suicide) on the HDRS-17;Having undergone or currently undergoing modified electroconvulsive therapy (MECT) or repetitive transcranial magnetic stimulation (rTMS) within the past month;Concurrent participation in another clinical trial or participation within 1 month prior to randomization is not allowed.

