### Sample size calculation

The sample size will be determined using G*Power 3.1, based on the findings of a a tDCS meta-analysis of adult patients with MDD [17]. In this study, active tDCS was found to be significantly more effective than sham tDCS for the reduction of depression severity (Hedges’ *g* = 0.743). For a power of 80% and an alpha level of 5%, a total sample size of 48 patients (24 in each group) is required to detect significant differences between the groups. To account for a 20% drop-out rate, a total of 58 patients (29 in each arm) will be recruited.

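### The plan does not clearly say which analysis and visit contrast is primary for HDRS-17 change, and no stated analysis uses baseline HDRS-17 as a covariate

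*Protocol article*

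**What the plan says.** Under Primary outcome, the protocol makes change in depressive symptoms the primary outcome and ties the HDRS-17 response and remission rates to 6 weeks after the intervention. The Abstract lists all three HDRS-17 measures as primary and gives several assessment times. Table 1 schedules HDRS-17 at screening and at T0 to T3. Read with the time levels named in the Statistical analysis section, these are baseline, end of treatment, and 2 and 6 weeks later.

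The Statistical analysis section then contains three relevant statements:

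- A general rule, placed straight after the descriptive summaries: "Between-group comparisons will be assessed using the Mann–Whitney *U* test for continuous variables". Categorical variables go to chi-square or Fisher tests.
- A rule for repeated continuous outcomes: "a mixed linear model will be employed, which includes the interaction between group (active versus sham) and time". Baseline is listed as one of the time levels.
- A closing rule: "The hypotheses will be tested using unpaired, two-tailed tests at a significance level of 0.05".

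The primary outcome is to be analysed by intention to treat with worst-case imputation. No covariate is named for any of these analyses. Eligibility requires "HDRS-17 scores ≥ 8 and ≤ 52", and remission is a score of 7 or less.

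**The concern.** Two things look open.

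First, HDRS-17 change meets the description in both the Mann–Whitney sentence and the mixed-model sentence. A group-by-time interaction over four time levels also contains more than one contrast, and the text does not pick one. If this stays open until the data are seen, the primary p-value becomes a matter of choice.

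Second, baseline HDRS-17 is already measured in everyone at T0, yet it enters no stated analysis as a covariate. Entry starts at 8 with a wide range above it, and there are at most 29 patients per arm, so some chance imbalance at baseline is to be expected. A change score does not fully remove such imbalance unless the regression of follow-up on baseline has slope 1. For remission the dependence on baseline is plain: a patient who enters at 8 remits with a 1-point fall, while a severely ill patient needs a large one. What is at stake is a wider confidence interval than the data require and a primary estimate more exposed to chance imbalance.

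**Working it through.** **The plan's own figure.** Inputs from the Sample size calculation section: g = 0.743, power 80%, alpha 5%, and "a total sample size of 48 patients (24 in each group) is required to detect significant differences between the groups". With a two-sample t test (noncentral t):

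- 24 per arm, one-sided 0.05: power 0.813
- 24 per arm, two-sided 0.05: power 0.712
- 30 per arm, two-sided 0.05: power 0.808

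The figure of 48 reproduces only one-sided, although the analysis section requires two-tailed tests. That is a separate matter. It is noted here only because the powers below are two-sided and so start below 80%.

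**Numbers analysed.** The protocol says "To account for a 20% drop-out rate, a total of 58 patients (29 in each arm) will be recruited". Completers after 20% drop-out: 58 × 0.8 = 46.4, or 23 per arm. If everyone is analysed under intention to treat: 29 per arm.

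**Unadjusted reference, two-sided.** t test: 0.693 at 23 per arm and 0.794 at 29. Mann–Whitney, taken at relative efficiency 0.955 (normal data): about 0.67 and 0.775.

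**Formulas.** Let r be the correlation between baseline and follow-up HDRS-17, with equal variances s² at both visits.

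- Variance of change: 2(1 − r)s²
- Residual variance after baseline adjustment: (1 − r²)s²
- Ratio, adjusted to change: (1 + r)/2

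With complete data and baseline means left free, the mixed-model contrast of follow-up minus baseline between groups is the change-score comparison. The protocol does not say which SD scales g, so both cases are shown:

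- A, g in follow-up SDs: effective effect g/√(2(1 − r)) for change and g/√(1 − r²) adjusted.
- B, g in change SDs: g for change and g/√((1 + r)/2) adjusted.

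Example at r = 0.5, where A and B coincide: 0.743/√0.75 = 0.858. At 23 per arm, power goes from 0.693 to 0.812.

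The correlation is not in the documents; r = 0.3 to 0.7 is an assumption. Each cell gives change-score power → adjusted power, with the gain in points.

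| r | A, 23/arm | B, 23/arm | A, 29/arm | B, 29/arm |
|---|---|---|---|---|
| 0.3 | 0.549 → 0.733 (18.4) | 0.693 → 0.863 (17.0) | 0.652 → 0.830 (17.8) | 0.794 → 0.932 (13.8) |
| 0.4 | 0.614 → 0.766 (15.2) | 0.693 → 0.837 (14.4) | 0.718 → 0.858 (14.0) | 0.794 → 0.913 (11.9) |
| 0.5 | 0.693 → 0.812 (11.9) | 0.693 → 0.812 (11.9) | 0.794 → 0.894 (10.0) | 0.794 → 0.894 (10.0) |
| 0.6 | 0.787 → 0.868 (8.2) | 0.693 → 0.786 (9.3) | 0.875 → 0.935 (6.0) | 0.794 → 0.874 (8.0) |
| 0.7 | 0.889 → 0.932 (4.3) | 0.693 → 0.762 (6.9) | 0.948 → 0.973 (2.5) | 0.794 → 0.854 (6.0) |

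The confidence interval shrinks by the factor √((1 + r)/2), from 0.81 at r = 0.3 to 0.92 at r = 0.7.

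**Simulation check** (24 per arm, case A, normal data). For r = 0.4, 0.5 and 0.6, the change score gave 0.637, 0.708 and 0.807, and adjustment gave 0.784, 0.815 and 0.874. The formula values at 24 per arm are 0.633, 0.712 and 0.804 for change, and 0.785, 0.828 and 0.883 adjusted. The formula therefore flatters adjustment by up to about 1 point.

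**The case against.** The strongest reply is that nothing conflicts. The Mann–Whitney sentence follows the descriptive summaries and does not name the primary outcome. The mixed-model sentence is the specific rule for repeated outcomes, and HDRS-17 is one. The 6-week timing under Primary outcome could supply the contrast. This reading is reasonable, so a reader who infers that the plan commits to two rival primary p-values goes further than the text. It is not the only reading, however. The sentence with Mann–Whitney also holds the only tests named for response and remission, so it is not confined to baseline tables, and the closing rule on unpaired tests fits those tests better than a mixed model.

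A second tempting inference is that the plan ignores baseline altogether. It does not. The mixed model has baseline as a time level, so its group-by-time contrast is a difference in change, and response is itself defined relative to baseline. The shortfall is one of efficiency, not validity.

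Third, a reader might assume an overall interaction test on 3 degrees of freedom and unconstrained baseline means. The protocol states neither. A model that constrains baseline means to be equal fits the same sentence and has essentially the efficiency of adjustment.

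Fourth, an article commonly leaves covariates to the full protocol or SAP. That is fair, and the absence of a covariate list alone would not be a finding. What stands is that the analysis as written leaves the primary test and contrast unclear, and that adding baseline as a covariate is a gain available at no cost.

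**Conclusion.** The point holds as a lack of clarity about the primary analysis plus an unused gain in precision. At 23 per arm, adjustment adds about 4 to 18 points of power over a change-score analysis. At 29 per arm it adds about 2.5 to 18, before any dilution by worst-case imputation. These ranges rest on assumed r = 0.3 to 0.7, equal variances, g = 0.743 and two-sided testing. The gain is large when r is low and small when r is high, so no single figure should be quoted as the cost.

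It would be wrong to say that the plan throws away planned power. The sample size rests on one standardised effect and mentions no covariate gain. The gap between stated and actual power comes from the one-sided calculation set against the two-tailed rule, and needs its own correction.

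**What to change.** Replace the general wording for HDRS-17 with one named primary analysis:

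- A mixed model of post-baseline HDRS-17 (T1 to T3) with baseline HDRS-17 as covariate, group, time and group-by-time. A model with all four visits and baseline means constrained to be equal is an equivalent choice.
- The primary result is the 1-degree-of-freedom group contrast at 6 weeks post-intervention, with its estimate and 95% CI.
- Response and remission analysed with adjustment for baseline HDRS-17, for example by logistic regression.
- Mann–Whitney kept as a sensitivity analysis.
- A sentence on how this fits the stated intention-to-treat and worst-case imputation rule: whether imputed values enter the primary mixed model, or the model uses observed data and worst-case imputation is applied elsewhere.

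The cost is wording only: no new data and no extra patients, since HDRS-17 is already collected at T0. The protocol sends significant changes to analyses to its ethics committee and then to the registry record, so the change should go that way and be dated before unblinding.

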### Primary outcome

The primary outcome will be the change of depressive symptoms. The clinical response rate and remission rate, as assessed by the HDRS-17 (17-item Hamilton Depression Rating Scale) at 6 weeks post-intervention were measured. The Chinese version of HDRS-17 has been validated for its psychometric properties and is commonly used to evaluate depressive severity in Chinese patients with depression symptoms [18]. The clinical response is defined as a ≥ 50% reduction from the baseline [19], and a score of 7 or less will be used as an indicator of remission [20].

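### Worst-case imputation, as worded, also covers the continuous HDRS-17 change; it costs power and makes the primary test sensitive to unequal drop-out

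*Protocol article*

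**What the plan says.** Under Primary outcome, the protocol article states: "The primary outcome will be the change of depressive symptoms". The same paragraph goes on to "The clinical response rate and remission rate, as assessed by the HDRS-17" at 6 weeks after the intervention. The Abstract and the Discussion list all three measures together as the depressive-symptom outcome.

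The missing-data rule, under Statistical analysis, is one sentence: "The primary outcome will be analyzed based on the intention-to-treat principle, with worst case imputation applied". It makes no distinction between the continuous and the binary measures. The next sentence reads "For repeated continuous outcomes, a mixed linear model will be employed", with a group-by-time interaction over four assessments. Table 1 schedules the HDRS-17 at all four, so the score fits that description. For simple comparisons the section names the "Mann–Whitney *U* test for continuous variables".

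Drop-out also appears under Sample size calculation: "To account for a 20% drop-out rate, a total of 58 patients (29 in each arm) will be recruited".

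**The concern.** For a binary outcome, counting a missing patient as a failure is conventional and easy to interpret. For a continuous score, filling every gap with one bad value treats an invented number as observed. The filled patients form a group at the poor end of the scale, which widens the distribution. Each arm's mean then depends on how many of its patients left as well as on how its patients fared.

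At equal drop-out the effect is diluted. At unequal drop-out, the gap in drop-out rates becomes a gap in mean scores even if treatment does nothing. The rule governs the primary comparison of a 58-patient trial that itself plans for 20% drop-out. The mixed model already named would need no filled-in values.

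**Working it through.** **Inputs from the protocol article.** Hedges' g = 0.743; 24 evaluable and 29 recruited per arm; 20% drop-out; 1:1 allocation; two-tailed tests at 0.05; HDRS-17 of 52 as the upper entry limit.

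**Assumptions not in the document.** SD 7; sham endpoint mean 13-16; drop-out unrelated to outcome; filled value w from 22 (about a baseline level) up to the worst observed score. A fill of 52 is shown only as an upper bound, because the article does not name it as the imputed value.

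**Step 1: the plan's own figure.** The plan says: "For a power of 80% and an alpha level of 5%, a total sample size of 48 patients (24 in each group) is required". By the noncentral t, 24 per arm at g = 0.743 gives 81.3% power one-sided and 71.2% two-sided. So 48 is reproduced only as a one-sided calculation, while the analysis section fixes two-tailed tests. That is a separate point, but it sets the comparator: 20% drop-out leaves 0.8 x 29 = 23.2 per arm, and two-sided power on observed data is then about 69-70%, not 80%.

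**Step 2: equal drop-out, true effect present.** With missing share q, arm mean m and filled value w:
- Difference after filling = (1 - q) x 0.743 x SD = 0.8 x 0.743 x 7 = 4.16 points, against 5.20 before.
- Variance in an arm = (1 - q) x SD² + q(1 - q)(w - m)².

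Example with sham mean 14 and active mean 14 - 5.20 = 8.80:
- w = 25: active 39.2 + 0.16 x 16.2² = 81.2; sham 39.2 + 0.16 x 11² = 58.6; pooled SD 8.36; d = 4.16/8.36 = 0.50; t-test power at 29 per arm about 46%.
- w = 52: active 39.2 + 0.16 x 43.2² = 337.8; sham 39.2 + 0.16 x 38² = 270.2; pooled SD 17.4; d = 0.24; t-test power about 15%.

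Simulated power over the assumed range, 29 per arm, 20% missing in each:

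| Analysis | Two-sided power |
|---|---|
| Observed data only (t-test) | 69-70% |
| Filled, Mann-Whitney | 39-53% |
| Filled, t-test, w from 22 to worst observed | 39-59% |
| Filled, t-test, w = 52 | 15% |

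A second set of assumptions (sham mean 14, baseline mean 22, SD 5 to 8) agrees. Power is 38-41% by t-test and 41-42% by Mann-Whitney with the worst observed score, 42-50% by t-test with the baseline score carried forward, and 68-70% on observed data.

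**Step 3: no true effect, unequal random drop-out.** The expected spurious difference is (q_sham - q_active)(w - m). With m = 13 and 10% v 30% missing, this is 0.2 x (25 - 13) = 2.4 points for w = 25 and 0.2 x (52 - 13) = 7.8 points for w = 52. Simulated false-positive rates at mean 13, SD 7:

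| Drop-out | Mann-Whitney | t-test | Observed data only |
|---|---|---|---|
| 10% v 30% | 18-26% | 16-43% (43% at w = 52) | about 5% |
| 10% v 20% | 8-10% | 8-16% (16% at w = 52) | about 5% |

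The rate falls as the filled value nears the arm mean. Carrying the baseline score forward, under the second set of assumptions, gives 12-18% at 10% v 30%.

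**Step 4: true effect, unequal drop-out.** Take sham mean 14, SD 5 and a true difference of 3.7. With 10% missing in active and 30% in sham, the raw difference becomes 5.3 (worst observed score) or 10.9 (w = 52). With 30% in active and 10% in sham, d falls to 0.06-0.09 across the three SDs (worst observed score), or reverses to between -0.22 and -0.31 (w = 52). The direction of the distortion follows the arm that loses more patients.

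**Limits.** The observed-data figures come from a t-test on completers, as a simple stand-in for the mixed model. The mixed model itself was not simulated. In it, earlier observed visits would stay and only missing visits would be filled, so the exact sizes could differ.

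**The case against.** Several stronger readings are tempting, and the document does not support them.

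- **That power collapses to about 15%.** This needs a t-test and a filled value of 52. The section names the Mann-Whitney test and a mixed model, not a t-test, and no value is specified. Under Mann-Whitney a 52 is only a top rank, and power is about 38-40%. The loss must also be measured from 69-70%, because part of the shortfall from 80% lies in the sample size and not in the imputation.
- **That the two analysis sentences contradict each other.** They do not. Filled-in data can be fed into a mixed model. The filling is unnecessary there and does harm, but the two rules can coexist.
- **That the rule always shrinks the effect.** It inflates the effect when sham drop-out is higher.
- **That the allowance for drop-out contradicts the imputation rule.** Recruiting 58 to cover drop-out from 48 is ordinary practice. It simply does not budget for dilution.

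It can fairly be said that the rule was meant for response and remission only, with the mixed model handling the continuous score. That is possible, but the sentence says the primary outcome, and the article names change as that outcome. It can also be said that a condensed article may leave the definition of the worst value elsewhere. That is accepted: the missing definition is not the point, and the loss appears under every same-direction definition tried. Finally, nothing in the document predicts a 10% v 30% split; it assumes a single 20% rate and reports no adverse-event difference in the pilot. The false-positive figures therefore show how fragile the rule is and do not forecast what will happen.

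**Conclusion.** The point holds in this form: as worded, worst-case filling applies to continuous HDRS-17 change, where it lowers power and lets unequal drop-out alone move the result. At the plan's own 20% drop-out, equal in both arms, power falls from about 69-70% to about 39-53% by Mann-Whitney. With no true effect, false positives rise from about 5% to about 8-10% at 10% v 20% drop-out and 18-26% at 10% v 30%.

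These sizes depend on the assumed SD, means, filled value and random drop-out. The direction of the power loss requires drop-out that is equal or higher in the active arm. The rule is not reliably conservative: more sham drop-out favours active treatment. For response and remission, counting missing as failure is conventional and is not criticised here.

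**What to change.** Reword the missing-data sentence so that:

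1. The main analysis of HDRS-17 change is the planned mixed model on all observed visits in all randomised patients, without single imputation.
2. Worst-case filling is limited to response and remission, with missing counted as failure in both arms.
3. A delta-adjusted or tipping-point sensitivity analysis for the continuous score shows how pessimistic the assumption about drop-outs must be before the conclusion changes.

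The cost is one sentence and one added sensitivity analysis. The downside is that the main analysis then relies on missing at random, an assumption that the sensitivity analysis examines but cannot prove. The change does not repair the two-sided power shortfall in the sample size, which needs its own correction.

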## Oversight and monitoring

### Composition of the coordinating center and trial steering committee

A research management group, consisting of the trial investigators, will be established to oversee the project’s governance and day-to-day operations. The group will meet on a monthly basis to assess progress and ensure that the study is being conducted in accordance with the requirements of research ethics approval. While the importance of a trial steering committee in upholding study conduct quality is recognized, financial limitations have prevented the establishment of such a committee. Nevertheless, this research will be carried out under the auspices of Zhenjiang Mental Health Center, where stringent research governance structures are in place to ensure the quality of study conduct.

